Malaysia has an estimated HCV prevalence of 1.9% among its adult population according to an opt-in screening campaign conducted in 2019 [10] and has a history of providing hepatitis C treatment in the public sector [11]. In 2019, Malaysia launched a 5-year national strategic plan for viral hepatitis control [12], and the country has been expanding HCV testing and treatment access to the primary care and community levels while actively engaging key populations in services for hepatitis care [11]. One group that the Malaysian Ministry of Health (MoH) would like to understand how to reach more effectively is men who have sex with men (MSM). Malaysia has a strong network of primary health clinics, which serve a large percentage of the population. However, due to considerable socioreligious stigma in Malaysia, MSM may be less likely than other population groups to regularly attend primary health services and therefore represent good candidates for HCV self-testing [13]. To explore the usefulness of HIV self-testing in Malaysia to reach key populations such as MSM, a pilot study offering HIV self-testing via an online platform (JomTest) was launched in November 2020, in partnership with the Malaysian AIDS Council (MAC) and the University of Malaya [14]. JomTest caters to people who identify as MSM, people who inject/use drugs (PWI/UD), transgender women, sex workers and persons engaging sex workers. These same groups may also be at high risk of contracting HCV; however, estimates for HCV prevalence among these groups in Malaysia are currently limited.

In the present study, we will integrate HCV self-testing with the existing online HIV self-testing platform, JomTest. We aim to evaluate the impact, acceptability, feasibility and cost of home-based HCV self-testing made accessible via an online platform in Malaysia.

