## Statistical methods

### Statistical methods for primary and secondary outcomes {20a}

Data will be analysed using R (version 4.1 or higher). A summary of the statistical analyses that will be completed by the endpoint is shown in Table 2. These analyses will be conducted among the group of participants who received the oral fluid-based HCV self-test with the control group and the group of participants who received the blood-based HCV self-test with the control group.

**Table 2 Tab2:** Statistical analyses to be completed by the endpoint

Endpoint	Statistical analysis methods
1.1 The number and the proportion of participants who report completing the HCV antibody testing in the intervention group 1.2 To assess whether the proportion of participants who report completing the HCV antibody testing in the intervention group is greater than that reported by the participants in the control group by a margin of 20%	Descriptive statistics: Calculation of proportions with 95% CI of the difference in proportions will be evaluated by using the R function prop.test from the “stats” package, which relies on Wilson’s score method. Test of proportions: Two-sided test with a margin of 20%, implemented with the R function “stats::prop.test” with the following hypotheses: *H*_0_: *p*_fo,*I*_ − *p*_fo,*C*_ ≤ 20% *H*_A_: *p*_fo,*I*_ − *p*_fo,*C*_ > 20% where proportions are defined as *p*_*x*,*y*_ [*x* = investigated outcome (fo, pt, ref, trt), *y* = element of {intervention, control}]) comparing the proportion of individuals reporting HCV test results in the intervention versus control groups and between intervention groups. The differences will be reported together with their confidence intervals and the *p*-value related to the statistical comparison mentioned above. The alpha level will be set at 0.025 (2 two-sided tests with an alpha level of 0.05, with the application of Bonferroni correction).
2.1 Number and proportion of HCV antibody-positive individuals made aware of their status in the intervention versus the control group	Descriptive statistics: Statistical testing comparing the numbers of individuals in the intervention versus control groups and between the intervention groups. For details, see the methodology described for endpoint 1.2.
2.2 Number and proportion of HCV antibody-positive individuals who are referred for and complete HCV RNA confirmatory testing in the intervention versus control group	

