2.3 Number and proportion of HCV RNA-positive individuals who begin treatment in the intervention versus the control group	
2.4 Analysis of survey responses using proportions and means	Descriptive statistics for survey responses (e.g. proportions, means), as appropriate for the type of response.
2.5 Cost per test completed and cost per person diagnosed (serology, RNA) in the intervention versus control groups	Ingredients-based cost calculation approach.

In a sensitivity analysis, a possible confounding in terms of the time of proband’s actions will be evaluated by analysing the proportions as events by means of Kaplan-Meier analyses with the advantage that dropouts are taken into account as censored values in addition.

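### Endpoints 2.1-2.3, as worded, apply a large-sample two-proportion interval to what may be a handful of antibody- or RNA-positive people per group, where its 95% label can fail badly

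*Protocol article*

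**What the plan says.** In the protocol article, section Statistical methods for primary and secondary outcomes {20a}, Table 2 gives this method for the primary endpoint: "Calculation of proportions with 95% CI of the difference in proportions will be evaluated by using the R function prop.test", with the remark "which relies on Wilson’s score method". The table directs endpoint 2.1 to the same method: "For details, see the methodology described for endpoint 1.2". The method cells for 2.2 and 2.3 are blank, which reads as one merged cell covering all three.

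The endpoints are worded with positives as the denominator. Endpoint 2.1 is "Number and proportion of HCV antibody-positive individuals made aware of their status in the intervention versus the control group" and endpoint 2.3 is "Number and proportion of HCV RNA-positive individuals who begin treatment in the intervention versus the control group"; endpoint 2.2 again refers to antibody-positive people. The section has each kit group compared separately with control, and Sample size {14} sets a minimum of 250 in each of the three groups.

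The only prevalence offered is in Background and rationale {6a}: "Malaysia has an estimated HCV prevalence of 1.9% among its adult population". The same section says the enrolled groups may be at high risk but that estimates for them are limited. Sample size {14} states that the secondary objectives are not powered. No small-sample method or minimum count is named for 2.1-2.3.

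**The concern.** A two-sample prop.test is a chi-square test with a normal-approximation interval for the difference. It needs a reasonable number of people in each denominator, and if only the positives are counted, each denominator may be a handful. The Wilson label could reassure an analyst wrongly: it describes the one-sample output of the function, not the two-group interval.

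At stake are the linkage outcomes. The Background says evidence on linkage to care after HCV self-testing is needed, and the Objectives include RNA confirmation and treatment start. A difference reported as 0 with an interval of 0 to 0, from five people in all, would tell a policy reader nothing true about precision. Nor should an interval labelled 95% cover the truth about six times in ten.

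**Working it through.** The plan states no expected count or precision for 2.1-2.3, so there is no figure of its own to reproduce.

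**Step 1. How many positives?** Inputs: 250 per group (Sample size {14}); 1.9% prevalence (Background; general adults). Uptake is not stated, so 40-100% is an assumption, and so are the 5% and 10% prevalences shown for range. Expected antibody-positives found = 250 × prevalence × uptake.

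| Prevalence | 40% uptake | 70% uptake | 100% uptake |
|---|---|---|---|
| 1.9% | 1.9 | 3.3 | 4.75 |
| 5% (assumed) | 5.0 | 8.75 | 12.5 |
| 10% (assumed) | 10.0 | 17.5 | 25.0 |

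RNA-positive people are a subset, so endpoint 2.3 has fewer.

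**Step 2. What the function computes.** With d = x1/n1 − x2/n2 and k = 1/n1 + 1/n2, the interval is d ± w, cut at −1 and +1, where

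w = 1.96 × √[p1(1−p1)/n1 + p2(1−p2)/n2] + min(0.5, |d|/k) × k.

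If x1 = n1 and x2 = n2 (or both are 0), then d = 0 and both terms of w are 0, so the interval is 0 to 0. The chi-square statistic is 0/0. Running the function in R 4.3.3 on 5/5 vs 2/2, 5/5 vs 5/5 and 4/4 vs 2/2 gave 0 to 0 and p = NaN each time.

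**Step 3. One case in full: 3 vs 2 positives, true proportions 90% and 60%, true difference 0.30.** These outcomes give intervals that miss 0.30:

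- 3/3 vs 2/2: 0 to 0. Probability 0.9³ × 0.6² = 0.2624.
- 3/3 vs 0/2: d = 1, w = 0.5 × 0.833 = 0.417, interval 0.583 to 1. Probability 0.9³ × 0.4² = 0.1166.
- 1/3 vs 2/2: d = −0.667, w = 0.533 + 0.417 = 0.950, interval −1 to 0.283. Probability 0.027 × 0.36 = 0.0097.
- 0/3 vs 2/2 and 0/3 vs 0/2: together 0.0005.

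The misses sum to 0.389 after rounding, so coverage is 61%.

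**Step 4. The same enumeration for other cases** (numbers of positives held fixed; true proportions are assumptions).

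| Positives | True proportions | Coverage of nominal 95% | Chance of a 0-to-0 interval |
|---|---|---|---|
| 3 vs 2 | 90/60 | 61% | 26% |
| 3 vs 2 | 90/80 | 50% | 47% |
| 3 vs 2 | 90/90 | 99% | 59% |
| 5 vs 2 | 90/80 | 60% | 38% |
| 2 vs 2 | 90/80 | 44% | 52% |
| 5 vs 3 | 90/60 | 82% | 13% |
| 5 vs 5 | 90/60 | 94% | 5% |
| 9 vs 5 | 90/60 | 91% | 3% |
| 9 vs 5 | 90/80 | 87% | 13% |
| 12 vs 12 | 90/60 | 95% | 0.1% |
| 12 vs 12 | 90/80 | 97% | 2% |

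**Step 5. A score-based alternative.** For 3/3 the Wilson limits are 0.439 to 1; for 2/2 they are 0.342 to 1. Newcombe's interval for the difference runs from −(1 − 0.439) = −0.56 to 1 − 0.342 = +0.66, where prop.test gives 0 to 0. With 2-5 positives per group and true proportions from 5% to 95%, Newcombe's lowest coverage is about 87%, and it never has zero width.

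**Step 6. All randomised participants as denominator.** Take 1.9% × 70% = 1.33% against 1.9% × 40% = 0.76%, with 250 per group. The prop.test interval then covers 98%, with a 0.5% chance of zero width.

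**The case against.** The best counter-argument concerns the denominator. The Methods paragraph of the Abstract counts participants who receive a positive result, complete RNA testing and start treatment. Sample size {14} speaks of higher numbers diagnosed, linked and treated. If these outcomes were analysed per randomised participant, step 6 shows prop.test would be adequate. This stands as a limit: the point applies to the endpoints as the Outcomes section and Table 2 word them. A reader might infer that the interval stays wrong however the denominator is settled; the figures do not support that.

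Second, two to five positives is not a protocol expectation. It uses a general-adult prevalence, assumed uptakes and a minimum group size, in a population the Background describes as possibly at high risk. A reader might take 4.75 as a ceiling; it is not one.

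Third, most of these intervals are very wide: when not degenerate they average roughly 113 to 156 percentage points over the size pairs and true proportions examined. It would be wrong to infer that the method generally makes sparse data look precise. The failures are concentrated in the zero-width case and a few extreme tables. The zero-width output is also conspicuous when the counts appear beside it.

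Fourth, the secondary objectives are declared unpowered. That tempers the consequence, but it is a statement about power. Low power should show as wide, valid intervals, and it does not excuse an undefined p-value.

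**Conclusion.** The point holds in a bounded form. As worded, 2.1-2.3 are proportions among positives, and the named function does not deliver the method the table attributes to it. If the counts are as low as the 1.9% figure implies, the nominal 95% interval can cover about 60% or less and can collapse to 0 to 0.

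A reader might take 61% as the worst case or as typical. It is neither: coverage is 44% for 2 vs 2 at 90/80, 94% for 5 vs 5 at 90/60, and 99% for 3 vs 2 at 90/90, where the interval still collapses 59% of the time. The size depends on three things the document does not give: key-population prevalence, testing uptake, and the true success proportions. At an assumed 5% prevalence and 40-70% uptake (about 5 to 9 positives) the problem shrinks but remains. At about 12 per group it largely disappears.

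The correction is worth making because it is nearly free and safe at any count. It concerns secondary endpoints only.

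**What to change.** For proportions among positives in 2.1-2.3, replace the reference to the endpoint 1.2 method in Table 2 with the following:

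- the counts in each group;
- an exact (Clopper-Pearson) or Wilson interval for each group's proportion;
- a score-based interval for the difference, either Newcombe or Miettinen-Nurminen;
- if a p-value is wanted, an exact test (Fisher or Boschloo).

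Newcombe's interval is built from Wilson limits, so it would also make the table's label true. Keep the planned comparison of each kit with control. Pooling the kits is not needed to repair the interval and would undo a deliberate choice to evaluate the two sampling methods.

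The cost is one table cell, a few lines of R, and intervals that will often be wider.

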### Outcomes {12}

The primary outcomes are the number and proportion of participants who report completing HCV antibody testing in the intervention group and to assess whether the proportion of participants who report completing HCV antibody testing in the intervention group is greater than that of the participants in the control group by a margin of 20%.

The secondary outcome measures are as follows: the number and proportion of HCV antibody-positive individuals made aware of their HCV status in the intervention versus the control groups. The number and proportion of HCV antibody-positive individuals who are referred to and complete HCV RNA confirmatory testing in the intervention versus the control groups. The number and proportion of HCV RNA-positive individuals who begin treatment in the intervention versus the control groups. The completion of the Likert scale rankings of ease of use that the participant report regarding the HCV testing process. The cost per test completed and the cost per person diagnosed (serology, RNA) in the intervention versus the control groups.

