#### Sample size {14}

The study will enrol a minimum of 750 participants who meet the inclusion criteria. There will be a minimum of 250 participants who receive an oral fluid-based HCV self-test, 250 participants who receive a blood-based HCV self-test and 250 participants in the control group. The study is powered to detect at least a 20% between-group difference in HCV antibody self-testing between the intervention group and the control group, based on 80% statistical power and an alpha level of 0.05. As this study is one of the first to explore the impact of an HCV self-testing distribution model, there are no references available to draw on for the expected difference in between-group uptake of antibody testing rates. The use of a 20% between-group difference in HCV antibody testing uptake is based on expert opinion, according to previous experiences with HIV self-testing and the increases in the uptake of testing seen with the use of HIV self-testing [15].

For the primary objective, the null hypothesis is that there is no significant difference in the proportion of individuals reporting HCV test results in the intervention versus control groups. The alternative hypothesis is that home-based HCV self-testing in the intervention group will significantly increase the proportion of individuals reporting HCV test results.

The study is not powered to detect significant differences in the secondary objectives. However, similarly to the primary objective, the null hypothesis would be no significant difference between the intervention versus control groups, with the alternative hypothesis being that home-based HCV self-testing will result in significantly higher numbers of HCV-infected individuals being diagnosed, linked to care and treated, making it a cost-effective approach to HCV case-finding and elimination.

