### Data collection and management

#### Plans for assessment and collection of outcomes {18a}

Participants will complete the baseline, follow-up #1 and follow-up #2 surveys via the online platform (supplementary annex 3). The baseline survey will assess participants’ current knowledge of hepatitis C, including risk factors for contracting hepatitis C, as well as gather information on their current behaviours that may be related to risk factors.

Follow-up survey #1, to be taken 2 to 4 weeks post-enrolment, will ask the participant to report if they have conducted the HCV test and, if so, to provide the results of the test. If the participant reports having taken the test, they will be asked to answer questions relating to their perception of the testing experience and what actions they took following their test result. If the participant reports that they have not yet taken the test, they will be asked questions about why they have not yet taken the test. This survey will also gather information from all participants on their current behaviours that may be related to risk factors for HCV.

Follow-up survey #2, to be taken 4 to 8 weeks post-enrolment, will ask the participant to report if they have taken the HCV test (if they have not already reported taking the test in follow-up survey #1) and, if so, to provide the results of the test. If the participant reports having taken the test, they will be asked to answer questions relating to their perception of the testing experience and what actions they took following their test result. If the participant reports that they have not yet taken the test, they will be asked questions about why they have not yet taken the test. For participants who reported taking the HCV test in follow-up survey #1, follow-up survey #2 will start by gathering information on what actions the person has since taken with regards to seeking further HCV care (if their HCV test was positive). This survey will also gather information from all participants on their current behaviours that may be related to risk factors for HCV.

Data relating to costs will be gathered from a provider’s perspective and will be obtained by conducting a desk review of the costs incurred in the study. These costs will include aspects such as human resources, shipping, and maintaining the online platform.

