### Methods in analysis to handle protocol non-adherence and any statistical methods to handle missing data {20c}

The primary analysis will be performed using an intention-to-test analysis. The follow-up and incentivisation methods described above will be used in an attempt to minimise missing data.

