## Discussion

### Limitations

The study has some important limitations that will be considered and described in the study report. The foremost of these is due to the fact that it is important not to mix different types of tests (oral vs blood) at the same timeframe within the same community which would likely create disruptions and potentially hamper the study, we were unable to enact a 3-arm trial. Rather, the study allocates one type of test kit for the first 250 participants randomised to the intervention group and another type of test kit for the next 250 participants randomised to the intervention group. The control group will be recruited throughout the length of the study to minimise any selection bias over time. Additionally, because enrolment will be conducted via an online platform, the study population will comprise individuals who have access to the Internet and are Internet literate. This may exclude individuals who could also benefit from HCV self-testing but who are unable to access the Internet. Uptake of testing in the control arm may be affected by the geographical location of the participant and the distance to their nearest testing centre. Moreover, the ongoing COVID-19 pandemic could affect the participants’ willingness to visit a healthcare facility, which may have a negative impact on the uptake of testing in the control arm and the uptake of treatment in both the intervention and control arms. Finally, the questionnaires have a multiple-choice design that may not capture some important context-specific aspects.

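### Censoring dropouts in the Kaplan-Meier sensitivity analysis is likely informative and shifts it towards a responder-only estimate; Table 2's kit groups should be worded by randomisation, not receipt

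*Protocol article*

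**What the plan says.** The primary outcome (Outcomes {12}) is "the number and proportion of participants who report completing HCV antibody testing in the intervention group", compared with control. It is collected by online survey: follow-up survey #1, at 2 to 4 weeks, "will ask the participant to report if they have conducted the HCV test", and survey #2, at 4 to 8 weeks, asks again (Plans for assessment and collection of outcomes {18a}). Table 2 analyses it as a difference in proportions with prop.test, against a 20% margin.

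On the analysis set, section {20c} states: "The primary analysis will be performed using an intention-to-test analysis". On dropouts, the paragraph after Table 2 adds a sensitivity analysis on the timing of participants' actions, to be done "by means of Kaplan-Meier analyses with the advantage that dropouts are taken into account as censored values in addition".

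The compared groups are worded in two ways. The lead-in to Table 2 speaks of "the group of participants who received the oral fluid-based HCV self-test with the control group" and words the blood kit comparison likewise; the sample size section also uses receipt: "There will be a minimum of 250 participants who receive an oral fluid-based HCV self-test". The Limitations section uses order of randomisation: "the study allocates one type of test kit for the first 250 participants randomised to the intervention group".

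**The concern.** Kaplan-Meier gives an unbiased estimate only if a censored person has the same later chance of the event as those still under observation. Here the event is seen only when the participant answers. A participant who answers nothing has no observed time after enrolment, so censoring removes that person from the risk set and in effect assigns the responders' uptake. Under an endpoint of reported completion the same person is a known non-event, so the censored curve also estimates something different from the primary analysis.

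It is plausible that people who did not test are less inclined to answer a survey about testing. The link may also differ by arm. Under Trial design {8}, controls who have not gone to a clinic are offered a self-test after the two surveys. If they know of this offer, untested controls have a reason to respond that untested intervention participants lack. The survey vouchers go to both arms and do not remove that difference.

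At stake is the credibility of the check. A reader would use this analysis to judge whether dropout matters, and it could either cast doubt on a sound primary result or appear to confirm a weak one.

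The wording on receipt is a smaller matter. Kits are mailed to one arm only, so a literal receipt-based group could lose people from that arm with no counterpart among controls.

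**Working it through.** The article states no uptake, survey response or kit delivery rate, so it has no figure of its own to reproduce. All rates below are assumptions. Only the 20-point benchmark comes from the document (Outcomes {12}, Table 2).

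**Step 1: what the censored curve estimates.** Let *u* be true uptake in an arm, *r_t* the response rate among testers and *r_n* the response rate among non-testers. Suppose never-responders are censored before survey #1 and all others answer both surveys. The two Kaplan-Meier steps then multiply out to the proportion among responders:

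- Censored Kaplan-Meier = *u·r_t* / [*u·r_t* + (1 − *u*)·*r_n*]
- All randomised, no report = not completed: *u·r_t*

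**Step 2: the two arm patterns, with *u* = 70% (intervention) and 50% (control).**

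- Response 90% in testers, 50% in non-testers. Intervention: 0.63 / (0.63 + 0.15) = 80.8%. Control: 0.45 / (0.45 + 0.25) = 64.3%.
- Response 90% in everyone. Intervention: 0.63 / 0.90 = 70.0%. Control: 0.45 / 0.90 = 50.0%.

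**Step 3: the differences (true difference +20.0 points).**

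| Response assumption | Censored Kaplan-Meier | All randomised |
|---|---|---|
| 80% in everyone, both arms | 70.0 − 50.0 = +20.0 | 56.0 − 40.0 = +16.0 |
| 90%/50% in both arms | 80.8 − 64.3 = +16.5 | 63.0 − 45.0 = +18.0 |
| 90%/50% in intervention only, 90% in control | 80.8 − 50.0 = +30.8 | 63.0 − 45.0 = +18.0 |
| 90%/50% in control only, 90% in intervention | 70.0 − 64.3 = +5.7 | 63.0 − 45.0 = +18.0 |

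With no true difference (50% in both arms) and the 90%/50% pattern in one arm only, the censored curve gives 64.3 − 50.0 = +14.3 or −14.3 points, while the all-randomised difference is 45.0 − 45.0 = 0.

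The first row also shows a limit of the alternative. Counting silence as not completed matches the endpoint of reported completion, but it understates actual testing when testers fail to report. An explicit sensitivity analysis is therefore still useful.

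**Step 4: what a direct analysis would show.** Take the both-arms row. Reported completion is 63% versus 45%, and non-response is 22% versus 30%. If *a* and *b* are the assumed uptakes among non-responders in the intervention and control arms:

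- Difference in points = 18 + 22*a* − 30*b*
- Bounds: *a* = 0, *b* = 1 gives −12; *a* = 1, *b* = 0 gives +40.
- Censoring amounts to *a* = 0.808, *b* = 0.643: 18 + 17.8 − 19.3 = +16.5.
- In this scenario the true values are *a* = 7/22 and *b* = 5/30: 18 + 7 − 5 = +20.

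Censoring is thus one hidden choice of *a* and *b*; a tipping-point analysis shows the whole range.

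**Step 5: receipt wording, if taken literally.** If a share *q* of kits is not received and uptake among recipients is *u*, uptake over everyone assigned is *u*(1 − *q*), so restricting to recipients adds *u·q*. With *q* = 2% and *u* = 50% this is 1.0 point; with *q* = 10% and *u* = 90% it is 9.0 points.

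**The case against.** Most of the opposing case stands and limits the point.

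- *The primary result is untouched.* A reader might infer that the trial's uptake difference is biased. The document does not support this: the primary comparison is prop.test under an intention-to-test label, and Kaplan-Meier appears only as a sensitivity analysis about timing, with no 20-point test attached to it.
- *Bias is not automatic.* It is zero when response is unrelated to testing, and the largest shifts above need the pattern in one arm only. All the rates are assumed.
- *Dropouts is not defined.* The article does not say that every non-responder is censored at day 0. Someone who answers survey #1 as untested and misses survey #2 contributes time at risk, and the term may mean withdrawals only. The responder-only formula is the case of never-responders censored at the start.
- *Confounding.* The text says timing will be evaluated, not that Kaplan-Meier will adjust for it. A display of time to testing is a reasonable use.
- *Receipt.* A reader might infer that undelivered kits are excluded. Nothing in the article describes confirming delivery or dropping anyone for non-delivery, and both the intervention description {11a} and the Limitations section define the kit groups by order within the intervention arm. Assignment was probably meant.
- *A fuller missing-data rule* may sit in the full protocol or analysis plan, so its absence from the article is no defect.

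What remains is that the article does name a way of handling dropouts and presents it as an advantage, although reporting and testing are plausibly linked.

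**Conclusion.** The point holds as a cheap improvement to a sensitivity analysis, plus a wording correction. Censoring dropouts is likely informative here, because the outcome is seen only through the reports that dropouts fail to give. Under assumed uptake of 70% versus 50% and the 90%/50% response pattern, a true 20-point difference shows as anything from +5.7 to +30.8 points, depending on which arm is affected. Neither the size nor the direction can be predicted from the document. This rests on three assumptions: the response rates, the reading of dropouts as including never-responders, and their censoring before the first survey.

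The receipt wording is an ambiguity, not a demonstrated exclusion. The 1.0 to 9.0 points in step 5 apply only if the literal reading were carried out.

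**What to change.** 1. State that the analysis set is everyone randomised, by assigned arm, with no reported completion counted as not completed. This spells out what the endpoint and the intention-to-test label already imply.
2. For the dropout check, replace the censored Kaplan-Meier by bounds or a tipping-point analysis in which the assumed uptake among non-responders varies separately by arm, as in step 4. Report which combinations change the conclusion against the 20-point benchmark.
3. Keep Kaplan-Meier only to describe time to testing, with non-reporters kept at risk to the end of the follow-up window (week 8, day 56).
4. In the lead-in to Table 2, replace the reference to kits received by randomisation to the intervention during the oral fluid kit period or the blood kit period.

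The cost is a few sentences and a few lines of code, with no new data. The downside is a little more analysis work and a range in place of one simple sensitivity estimate.
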